#### Cluster 4: Eating behavior

For psychological assessment of eating behavior the inventory of eating and weight problems for children (EWI-C)
[78] will be used, in addition, also a specific questionnaire asking for their food preferences and regular eating behaviors at home.

To validate eating behavior as indicated in the questionnaire, children will be allowed a 20-minute post-stress recovery (see above) while watching a movie on TV and taking snacks of different caloric density ad libitum, with the experimenter not present during that time. However, unbeknown to the children the snack plate will be filmed during this period. In addition, food will be weighted before and after the session and consumed calories will be calculated. In addition, some of the children will carry a novel "bite-counter" (Bite Technologies, Pendleton, South Carolina, USA)
[66,101] that registers the numbers of arm and hand movements typical for eating behavior. Video-recordings will be used to validate the bite counting technology, as well.

Furthermore, the cognitive ability to discriminate volumes of food and liquids will be tested. Therefore, pairs of glasses (e.g. low, wide glass versus a slim, tall glass), of plates and bowls with pre-defined amounts of water or uncooked lentils (representing food) will be presented. The children and adolescents will be asked to estimate the quantities of the provided amounts. They will also be asked to estimate the amount of food needed to satisfy normal hunger.

### Ethics and registration of the study

The study protocol was approved by the Ethics Committee of the medical faculty for the University Tübingen, Germany. This study is registered at the German Clinical Trials Register (DRKS) with the clinical trial number DRKS00005122. The DRKS is an approved primary register in the WHO network. Children and parents were informed about the study purpose during the admission interview by a physician or therapist and were asked to provide written consent prior to inclusion.

### Statistics

We expect measures to be highly correlated within each cluster, and some variables within each cluster to be more sensitive or predictive to weight-loss during treatment than others. These key variables have been used as predictors for sample size calculation.

Cluster 1: Key variable: self-esteem scale according to Rosenberg

Cluster 2: Key variable: agility/motor activity (Dordel-Koch test)

Cluster 3: Key variable: ECG/IBI response to stress

Cluster 4: Key variable: caloric intake per time unit

To calculate optimal sample size, G*Power 3.1.7
[102] was used. To analyze the main research question (prediction of weight loss maintenance by key variables), sample size was derived for r^2^ deviation from zero (F distribution, Linear multiple regressions: Fixed model, R^2^ deviation from zero). Correlations of r = .3 (medium effect size
[103]) were assumed for predictor-outcome associations as well as the predictor‘s intercorrelation matrix, resulting in a squared multiple correlation of r^2^ = .189 and an f^2^ = .234. With a level of significance at alpha = .05 and a statistical power (1-beta) of .8, a sample size of 57 would be optimal to decide on the predictive quality of the model.

Statistical analysis will be conducted in two steps: variables within each cluster will be tested for their intercorrelation, their responsiveness to weight change, and for their ability to predict weight loss in a one-by-one fashion (step 1). In cases of high within-cluster intercorrelation (as predicted), a hierarchical model will be constructed with the most sensitive variable per cluster to be entered into a multivariate regression model (step 2).

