**Methods/Design:**

Over a one year period, 60 obese children and adolescents between 9 to 17 years of age shall be recruited at an inpatient children rehabilitation facility in Germany. They will be investigated twice within a few days following admission and prior to discharge. The study will be an integrated component of an established inpatient weight-loss and in part psychosomatic therapy. The collected data can be grouped into four clusters: 1) demographic, sociometric and psychometric data, 2) objective and subjective parameters of body condition, 3) autonomic nervous system regulated functions and 4) objective and subjective parameters for eating behavior. Primary outcome is the change of the body mass index standard deviation score (BMI-SDS). In order to evaluate the data appropriately, all examinations will be also conducted in a normal-weight reference group, matched for age and gender.

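### Rejecting R² = 0 with 57 children shows association only; neither the test nor the size can decide the model's predictive quality, as the Statistics section says.

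*Protocol article*

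**What the plan says.** All of this stands in the Statistics section of the protocol article, apart from the recruitment figure.

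- One key variable is named for each of four clusters, and "These key variables have been used as predictors for sample size calculation".
- The test is the overall F test of a multiple regression: "sample size was derived for r^2^ deviation from zero (F distribution, Linear multiple regressions: Fixed model, R^2^ deviation from zero".
- Correlations of .3 "were assumed for predictor-outcome associations as well as the predictor‘s intercorrelation matrix", "resulting in a squared multiple correlation of r^2^ = .189 and an f^2^ = .234".
- The error rates are given as "With a level of significance at alpha = .05 and a statistical power (1-beta) of .8".
- The conclusion drawn is that "a sample size of 57 would be optimal to decide on the predictive quality of the model".

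The Abstract (Methods/Design) says that "60 obese children and adolescents between 9 to 17 years of age shall be recruited". The Statistics section words the main question as one of prediction, and the Discussion hopes that some parameters may serve for screening in future care.

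**The concern.** The F test of R² = 0 and the predictive quality of a model are different things. The test asks whether at least one coefficient is non-zero in the population. Predictive quality asks how close the fitted model's predictions come to the outcomes of children who were not used to fit it. A model can pass the first and do poorly on the second, and with 57 children and four coefficients this is not unusual. A sample size derived for the first question is not thereby sized for the second.

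This matters because prediction is the purpose of the study. Under Aims of the study, the article sets out to identify pre-treatment predictors of weight loss, and screening use depends entirely on performance in new children. Read as written, the sentence invites a significant F test to be taken as evidence that the model predicts well. The problem exists even if the four key variables are fixed in advance, so it does not depend on how variables are selected.

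**Working it through.** **Inputs.** Four predictors, all correlations .3, alpha .05, power .80 and N = 57 (Statistics); recruitment of 60 (Abstract).

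**1. Reproduce the plan's figure.**
- R² with four equally correlated predictors: 4 × .3² / (1 + 3 × .3) = .36 / 1.9 = .1895.
- f² = .1895 / (1 − .1895) = .2338. Both match the article.
- Fixed-model power from the noncentral F distribution with df 4 and N − 5 and noncentrality f² × N: .7999 at N = 56 and .8086 at N = 57. So 57 reproduces. (With f² rounded to .234, 56 already gives .8004.)
- If the predictors are treated as random, as measured variables are, power at N = 57 is about 79%.

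**2. What significance requires.** The critical F(4, 52) is 2.55, so the smallest significant sample R² is 4 × 2.55 / (4 × 2.55 + 52) = .164.

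**3. Expected R² in new children.** For multivariate normal data with p fixed-in-advance predictors, the mean R² in new children, defined as 1 − MSE / Var(y), is

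1 − (1 − R²)(1 + 1/N)(N − 2)/(N − p − 2).

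At R² = .1895, N = 57 and p = 4 this is 1 − .8105 × 1.0175 × 1.0784 = .111.

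**4. In-sample against new children.** Simulation under the plan's correlations, 40,000 samples for each N:

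| Setting | In-sample R² | R² in new children | Ratio |
|---|---|---|---|
| N = 57, all samples, raw R² | .241 | .111 | 2.2 |
| N = 57, all samples, adjusted R² | .183 | .111 | 1.65 |
| N = 57, significant samples, raw R² | .275 | .110 | 2.5 |
| N = 60, all samples, raw R² | .241 | .115 | 2.1 |
| N = 60, significant samples, raw R² | .269 | .114 | 2.35 |

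Among significant samples at N = 57, about 34% of models have an R² below .10 in new children, and 4 to 5% have one at or below zero.

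**5. If the true R² is not .189.** These values are assumptions; the documents give none but .189.
- True R² .10: the step 3 formula gives 1 − .90 × 1.0175 × 1.0784 = .012. About 45% of studies would be significant, and the mean R² in new children among those is about zero.
- True R² .25, .30 or .40: the approximate raw ratio over all samples falls to 1.7, 1.5 and 1.3.
- By the same formula, the mean R² in new children is zero when the true R² is 1 − 1/(1.0175 × 1.0784) = .089.

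**6. Precision.** An observed raw R² of .189 at N = 57 has a 95% confidence interval of about 0 to .35 (random-predictor distribution inverted). The study could not separate a model of no use from a moderately good one.

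**7. Data-driven selection.** The Statistics section also describes choosing the most sensitive variable per cluster in the same data. With an assumed 3 to 10 equally good candidates per cluster and within-cluster correlations of .5 to .9, the ratio over all samples is 2.5 to 3.3. The fixed-predictor figures above are therefore the milder case.

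**The case against.** The strongest reply is that the article names its test openly, so a reader can see what 57 is powered for. The disputed words close a sample-size paragraph; they are not a formal decision rule. For an exploratory aim, an overall association test is a conventional basis for sample size, and overfitting is a property of every small regression. The article is also a condensed account, and internal validation, confidence intervals for R² and prediction error are commonly left to a full protocol or SAP.

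Much of this stands and limits the point:

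- A reader might infer that the sample size is miscalculated. It is not; 57 reproduces.
- A reader might infer that the plan has no validation step. The fuller documents are not shown, so this cannot be said and is not charged.
- A reader might infer that the reported R² will overstate prediction 2.5-fold. The article does not say whether raw, adjusted or corrected R² will be reported, and 2.5 applies only to raw R² in significant samples at a true R² of .189 and N = 57.
- A reader might infer that a significant model is likely to be worse than the mean. At the plan's own R² this happens in only 4 to 5% of significant samples; it becomes common only if the true R² is much lower.

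What does not stand is that the sentence is harmless. It states what the sample size can decide, and an SAP could not make an F test of R² = 0 into a measure of prediction.

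**Conclusion.** The point holds as a wrong inference stated in the text, not as an arithmetic error or an omission. The calculation supports a test of association, and the article claims a decision on predictive quality. Under the plan's own assumptions, with four pre-fixed predictors, normal data and a true R² of .189, a raw in-sample R² would on average be about twice what the model achieves in new children. Significance would leave about a one-in-three chance that the model explains less than 10% there. The multiplier depends strongly on the true R² and on which R² is reported, so it should not be quoted without those conditions. The data themselves remain valid; only the conclusion attached to the test and the sample size is unsupported.

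**What to change.** Restate the sentence along these lines: with four predictors and all correlations equal to .3, 57 children give about 81% fixed-model power (about 79% with random predictors) to reject R² = 0 at alpha .05.

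Base any statement on predictive quality on a bootstrap or cross-validated optimism-corrected R² with its 95% confidence interval, together with the prediction error in BMI-SDS units. If the within-cluster selection of step 1 is used, repeat it inside each resample. Do not call the model predictive on the F test alone, and say which R² is being reported.

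This needs no more children, visits or measurements. It costs one sentence, a little more analysis, and a reported figure that will look less favourable.

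### The sample size is set for four pre-named predictors, but the analysis enters the variable that looks best in each cluster after screening on the same children, so the stated alpha and power do not carry over

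*Protocol article*

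**What the plan says.** All the relevant text is in the protocol article, mainly under Statistics.

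- Four key variables are named, one per cluster: the Rosenberg self-esteem scale, the Dordel-Koch motor test, the ECG/inter-beat-interval response to stress, and caloric intake per unit of time. Of these it says "These key variables have been used as predictors for sample size calculation".
- The calculation is for "Linear multiple regressions: Fixed model, R^2^ deviation from zero". The effect size starts from "Correlations of r = .3 (medium effect size", used both for predictor with outcome and for predictor with predictor. The error rates are "With a level of significance at alpha = .05 and a statistical power (1-beta) of .8", and the conclusion is that "a sample size of 57 would be optimal to decide on the predictive quality of the model".
- In step 1 the variables in each cluster are examined for correlation with one another, for response to weight change, and for "their ability to predict weight loss in a one-by-one fashion (step 1".
- In step 2, where correlation within clusters proves high, "a hierarchical model will be constructed with the most sensitive variable per cluster to be entered into a multivariate regression model (step 2".
- The Abstract gives the sample: "60 obese children and adolescents between 9 to 17 years of age shall be recruited". The 30 normal-weight children described under Control group supply reference values and cannot validate the model.
- The sample-size paragraph names maintenance of weight loss as the main question. Step 1 screens on weight loss. The Primary outcome section defines BMI-SDS change from measurements at admission and discharge.

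**The concern.** A fixed-model F test has its nominal error rate only when the predictors are chosen without looking at the outcome. Choosing the best of several candidates in each cluster by their relation to weight loss, and then testing the chosen four against weight loss in the same children, uses the data twice. Chance associations that survive screening are counted again as evidence, and R² is inflated for the same reason. The article would then describe one procedure in its sample size and carry out another. The Discussion hopes that some measures may become screening tools for tailoring therapy, so a falsely significant model or an optimistic R² could influence that use.

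**Working it through.** **Step 1. Reproduce the plan's figure.** The inputs from Statistics are k = 4 predictors, r = .3 with the outcome, ρ = .3 between predictors, alpha .05 and power .8.

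- R² = k·r² / (1 + (k − 1)·ρ) = 4 × .09 / (1 + 3 × .3) = .36 / 1.9 = .1895 (plan: .189).
- f² = R² / (1 − R²) = .1895 / .8105 = .2338 (plan: .234).
- Power comes from the noncentral F distribution with λ = N·f² and degrees of freedom 4 and N − 5. N = 56 gives .7999, N = 57 gives .809 and N = 60 gives .833.

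The stated 57 is correct for four predictors fixed in advance.

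**Step 2. Reference values at n = 60 with no association.** The critical F(4, 55) at 5% is 2.54. This corresponds to R² = 4 × 2.54 / (4 × 2.54 + 55) = 10.16 / 65.16 = .156. The expected R² from noise with fixed predictors is 4/59 = .068.

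**Step 3. Null simulation with selection.** The setting is n = 60 and 4,000 simulated trials per cell. In each cluster the variable with the largest absolute correlation with the outcome is kept, and the ordinary four-predictor F test is run at .05 on the same outcome. The article gives neither the number of candidates nor the within-cluster correlation, so both are assumptions. Between-cluster correlation is set at .3. The row 6/14/7/6 is a rough count of the measures listed for clusters 1 to 4. The Monte Carlo standard error is at most √(.25/4000) = .008.

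Each cell shows the rejection rate, with mean R² in parentheses.

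| Candidates per cluster | within-cluster corr. .5 | .7 | .9 |
|---|---|---|---|
| 1 (fixed in advance) | 5.6% (.068) | 5.0% (.068) | 4.9% (.067) |
| 3 | 21.7% (.119) | 18.7% (.111) | 11.9% (.093) |
| 6/14/7/6 | 52.2% (.166) | 42.0% (.150) | 21.8% (.116) |
| 10 | 58.6% (.175) | 48.5% (.160) | 25.0% (.124) |

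Mean R² from noise after selection is therefore about .09 to .18, against .07 for fixed predictors. Using n = 57 instead raises these R² values by about .01 and leaves the rejection rates essentially unchanged.

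**Step 4. Selection on one outcome, test on another.** Suppose screening uses in-treatment weight loss and the final model predicts later maintenance. With 6/14/7/6 candidates and within-cluster correlation .7, the type I error depends on the correlation between the two outcomes:

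| Correlation between outcomes | 0 | .3 | .5 | .7 |
|---|---|---|---|---|
| Type I error | 4.8% | 7.2% | 11.8% | 19.1% |

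**The case against.** **The most sensitive variable may simply mean the named key variable.** The section introduces the four as variables expected to be more sensitive or predictive than others, so this reading is possible. But the one-by-one screening would then play no part in building the model. The two readings have very different error rates and the text does not choose between them.

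**The selection rule simulated is not in the article.** Step 1 lists three criteria, and the largest correlation with the outcome is only one way to apply them. This stands as a limit on the figures.

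**High within-cluster correlation limits the damage.** This is largely right. Step 2 is conditioned on it, so the right-hand column of the table is closer to what the article expects. Inflation is smaller there but not absent: three candidates at .9 still give about 12%.

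**The tested outcome may differ from the screened one.** This also stands, and step 4 of the working shows how much it lowers the inflation. The Statistics section does not separate the two outcomes.

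**The study is exploratory, and corrections may sit in a plan not shown.** The stated aim is to find potential predictors, and unadjusted screening is ordinary in that setting. The missing multiplicity or resampling details are therefore not the point here. The point is that the article attaches alpha .05 and power .8 to one model and describes fitting another.

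A reader might go further and infer that a model of pure noise would usually be significant, or that noise alone yields the R² of .189 for which the study is powered. Both need about ten or more candidates in every cluster and only moderate correlation, and the article supports neither as its expected case. A reader might also infer that the selected model's p-value will certainly be reported uncorrected. The article does not say so.

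**Conclusion.** The concern holds in conditional form. The sample-size arithmetic is sound, but it belongs to a fixed four-variable model, and the analysis as written lets the data choose the four. If the chosen variables are tested with the ordinary F test on the outcome used to choose them, the nominal 5% becomes roughly 12–22% with three candidates per cluster, 22–52% on the rough count of listed measures, and 25–59% with ten. These ranges run over within-cluster correlations from .9 down to .5. Apparent R² is overstated as well. If screening uses in-treatment weight loss and the test concerns maintenance, the error rate is about 5–19% for outcome correlations of 0 to .7. All these sizes rest on assumed candidate counts, correlations and selection rule. The direction of the bias under same-outcome selection does not depend on the particular values, provided the candidates within a cluster are not interchangeable.

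**What to change.** In Statistics, state that the confirmatory step-2 model is the regression on the four variables already named, whatever step 1 shows. State also which outcome it tests: BMI-SDS change from admission to discharge, which is the primary outcome, or weight-loss maintenance, which is the question the sample size names. With the predictors fixed, 57 children with data on that outcome give power .81 under the planning assumptions, and 60 give .83.

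Label step 1, and any model containing data-selected variables, exploratory. Report the R² of such a model with bootstrap or cross-validation that repeats the per-cluster selection inside every resample.

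The cost is a few sentences and a few hours of programming, with no added children, measurements or visits. The one loss is that a variable discovered in step 1 cannot carry the confirmatory claim.

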#### Demographic, sociometric and psychometric predictors

It is known that in general the social environment of the child plays a crucial role in weight control
[18,19]. This applies to aspects such as ethnic origin
[20], income
[21], health of parents
[22] as well as their eating habits
[23]. The EvAKuJ study showed - in a sample of 1916 overweight and obese children and adolescents - that in inpatient treatments only the BMI at admission was predictive of the short and long-term treatment success, whereas gender, all collected psychosocial variables and the parental BMI played no significant role
[24].

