## Methods/Design

### Aims of the study

The aim of the study is to identify potential pre-treatment predictors of successful weight loss in obese children and adolescents during a standardized therapeutic treatment in an inpatient rehabilitation setting. In addition, repeated measures of the same variables at the end of treatment may demonstrate whether psychophysiological measures that respond to weight loss are associated with therapy success and whether they may serve to predict long-term weight-loss maintenance at follow-up. In addition, clinical parameters will be taken from the hospital charts and examined as potential predictor variables. We are aware that for some of the collected parameters the time span between measures may be too short. Therefore, follow-up studies are planned for evaluating the success of intervention.

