### Study population

#### Patients and the inpatient setting

The obesity therapy concept at the Children Rehabilitation Hospital for Respiratory Diseases, Allergies and Psychosomatics, Wangen i.A., Germany is aimed at recovery from comorbid diseases associated with obesity, rediscovering joy of life, developing a forward-looking perspective, independent living, and growing up unencumbered. The children and young people are treated in accordance with the latest developments in medicine, especially pediatrics and in close cooperation with regional educational institutions such as the obesity academy (Adipositas-Akademie Baden-Württemberg e.V.), an atopic dermatitis academy (Neurodermitisakademie München/Wangen/Gaißach) and an asthma academy (Asthmaakademie Baden-Württemberg e.V.). Infants, children and adolescents are housed and cared for in small therapeutic groups with peers of the same age and in residential units situated on a park-like hospital ground. The clinic has its own kindergarten and a school with regular classes for all types of curricula.

Pediatricians, allergists, psychologists, social workers and nursing staff, teachers, trainers, dietetic professionals, occupational and speech therapists and staff for physical therapy work together as one team. The special obesity training is an integral part of therapy. The individual modules of the training are rooted in the concept of the clinic, including exercise and sports, change to a healthy diet, and weight-loss.

The nutrition concept is based on a balanced diet or “optimized mixed diet”. In nutrition training, patients meet weekly in small groups of 6–8 age-matched participants. In a training kitchen, all children and adolescents learn how to prepare food and cook with the aim of proper food handling and preparation when they return home. Additionally, they complete "shopping training" in a supermarket.

The hospital treats approximately 200 obese children and adolescents per year. The average duration of stay is 42 days.

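### The step-2 model guarantees no place for admission BMI-SDS, so a key variable that only tracks baseline weight could be reported as a psychophysiological predictor

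*Protocol article*

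**What the plan says.** All references are to the protocol article.

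- **Statistics, analysis:** step 1 screens the variables within each cluster. Step 2 is described as hierarchical and takes "the most sensitive variable per cluster to be entered into a multivariate regression model (step 2"). No baseline term is named.
- **Statistics, sample size:** four key variables are listed, one per cluster (Rosenberg self-esteem, Dordel-Koch test, ECG/IBI response to stress, caloric intake per time unit). "These key variables have been used as predictors for sample size calculation". The test is "F distribution, Linear multiple regressions: Fixed model, R^2^ deviation from zero", and with "a statistical power (1-beta) of .8, a sample size of 57 would be optimal".
- **Demographic, sociometric and psychometric predictors:** in the cited study of 1916 children, "in inpatient treatments only the BMI at admission was predictive of the short and long-term treatment success". Gender, parental BMI and the psychosocial variables collected there played no significant role.
- **Primary outcome:** change in BMI-SDS, from weight and height measured at admission and discharge.
- **Aims of the study:** "clinical parameters will be taken from the hospital charts and examined as potential predictor variables". No cluster is assigned to them.
- **Cluster 2:** anthropometry, including a scale, belongs to the same cluster as the Dordel-Koch test.
- **Patients and the inpatient setting:** "The average duration of stay is 42 days". No spread is given.

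**The concern.** The study looks for psychophysiological predictors that might later serve as screening instruments. Such a predictor is useful only if it says more than the child's weight at entry already says.

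Under the step-2 rule as written, weight could enter only by winning the single place of cluster 2, and it would then displace motor performance. Chart variables have no stated route into step 2. So admission BMI-SDS and the four key variables are not assured of being in one model together. Motor performance, self-esteem and snack intake may well vary with admission BMI-SDS. If they do, and if baseline is related to change, a significant overall R² cannot be told apart from a restatement of baseline.

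**Working it through.** **1. The plan's own figure.** Inputs from Statistics: four predictors, all predictor-outcome correlations .3, all intercorrelations .3, alpha .05.

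- With equal correlations, R² = 4r² / (1 + 3 × .3) = 4 × .09 / 1.9 = .1895.
- f² = .1895 / (1 − .1895) = .2338.
- Noncentral F with 4 and N − 5 degrees of freedom, noncentrality f² × N: power is .809 at N = 57 and .833 at N = 60.

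The stated 57 is reproduced. It is the size for the overall R² of four key variables without covariates.

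**2. Proxy check.** Assume the key variables relate to outcome only through admission BMI-SDS. Let a be the key-baseline correlation and b the baseline-outcome correlation; neither is in the documents. Each key variable then has correlation a × b with outcome, and the unadjusted model has R² = 4(ab)² / 1.9, with intercorrelations kept at .3.

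| a | b | ab | R² | rejection at N = 57, nominal 5% |
|---|---|---|---|---|
| .1 | .3 | .03 | .0019 | 5.5% |
| .2 | .3 | .06 | .0076 | 7.1% |
| .3 | .3 | .09 | .0171 | 10.0% |
| .4 | .4 | .16 | .0539 | 24% |

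At the extreme of .5 and .5 the rate is 60%. At N = 60 the rates are slightly higher (10.3% for .3 and .3).

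**3. What adjustment does to power.** Test the R² increase from the four key variables after one baseline covariate, with 4 and N − 6 degrees of freedom. Hold the total key-outcome correlation at the protocol's .3. Then:

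- Increase in R² = 4(.3 − ab)² / (1.9 − 4a²).
- f² = increase / (1 − b² − increase).

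| a | b | R² increase | f² | power at N = 57 |
|---|---|---|---|---|
| 0 | 0 | .189 | .234 | .81 |
| 0 | .3 | .189 | .263 | .86 |
| .1 | .3 | .157 | .208 | .75 |
| .2 | .3 | .132 | .170 | .66 |
| .3 | .3 | .115 | .144 | .57 |
| .4 | .4 | .062 | .080 | .33 |

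Example for a = b = .3: 4 × (.3 − .09)² / (1.9 − .36) = .1764 / 1.54 = .115, and f² = .115 / (1 − .09 − .115) = .144.

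Adjustment raises power only in the second row, where baseline predicts outcome but is unrelated to the key variables. In the rows where a proxy problem can exist, power for the increment falls.

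**The case against.** **The omission is not absolute.** Chart parameters will be examined as predictors, weight can compete within cluster 2, and the word hierarchical could cover a first block. A condensed article may also leave the covariate list to a fuller plan. This stands in part, and it is why the point is that baseline has no guaranteed place. But the article does state what enters step 2, and its sample size test matches that content: an overall R², not an increase over covariates.

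**The correlations are assumed.** This stands. The Background gives no effect size for admission BMI, and its finding concerns BMI, not BMI-SDS. The section on predictors also says that clinical variables, including actual weight, have shown little predictive ability. With weak links the inflation is only one or two percentage points.

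**Stronger readings that the documents do not support.**

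- A reader might infer that leaving out baseline costs power. That holds only if baseline is nearly unrelated to the key variables, and then there is no proxy problem. Under the correlations that the proxy argument needs, adjustment lowers power for the key variables.
- A reader might infer that adjusting is therefore free. It is free in data but not in power, as step 3 of the working shows.
- A reader might put length of stay beside baseline as a missing covariate. The article gives only a mean of 42 days, with no spread and no stated link to outcome, so no share of variance can be derived. Realised stay is also unknown at admission, while the aim concerns pre-treatment predictors.

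**Conclusion.** The point holds for admission BMI-SDS. The protocol's own cited evidence names admission BMI as the one predictor of success in inpatients, the value is available for every child, and the step-2 rule does not secure it a place next to the key variables.

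The size depends on correlations that the documents do not give. False rejection by the overall F test at N = 57 is about 5.5% to 7% with weak key-baseline links (.1 to .2, baseline-outcome .3), 10% at .3 and .3, and 24% at .4 and .4. These figures assume no own effect of the key variables and intercorrelations of .3.

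The sample size calculation is correct for the test it names, but its 80% power applies only to the unadjusted overall R². It says nothing about prediction beyond admission BMI-SDS.

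**What to change.** In Statistics, state that admission BMI-SDS enters as the first block of the hierarchical model and the four key variables as the second. Report the R² increase from the second block, with its F test, alongside the unadjusted R². Length of stay may be added as a sensitivity adjustment only.

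Cost: no new measurement and one residual degree of freedom (power .809 to .808 if baseline is unrelated to everything). The real price is interpretive. With key-outcome r held at .3 and baseline-outcome r of .3, power for the increment at N = 57 is about .75, .66 and .57 for key-baseline correlations of .1, .2 and .3. The protocol should state this and restrict its 80% claim to the unadjusted test. More children need not be enrolled for it: a non-significant increment should simply be read with that power in mind.
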